## Abstract

**Background:**

Vitamin K antagonists (VKA) such as warfarin or phenprocoumon have been the mainstay of therapy for long‐term oral anticoagulant therapy (OAT) in patients with atrial fibrillation or with pulmonary embolism. Due to interferences with matrix Gla‐protein, an important vitamin K‐dependent local calcification inhibitor in cardiovascular structures, VKA antagonists stimulate cardiovascular calcification (CVC). In contrast, rivaroxaban, a nonvitamin K‐dependent oral anticoagulant (NOAC), should be neutral in terms of CVC. We seek to investigate these potential differences in CVC development between VKA versus NOACs in a randomized controlled trial (RCT).

**Methods:**

The influence of rivaroxaban compared to vitamin K antagonist treatment upon development of cardiovascular calcification in patients with atrial fibrillation and/or pulmonary embolism trial (NCT02066662) is a multicenter, prospective RCT with a two‐arm, open‐label study design. The primary endpoint is the progression of coronary and aortic valve calcification (quantified as calcification volume score) as assessed by cardiac computed tomography (CT) at 24 months in patients either treated by rivaroxaban or VKA. A total of 192 patients were randomized in a 1:1 fashion. The main inclusion criteria were the presence of atrial fibrillation and/or pulmonary embolism with the indication for OAT and pre‐existent coronary calcification. The development of CVC will be assessed by follow‐up CT at 12 and 24 months.

**Results:**

In total 192 patients (median age 70, 72% male) were enrolled over a period of 5 years and followed up for 2 years.

## INTRODUCTION

1

Atrial fibrillation is one of the most frequent indications for long‐term oral anticoagulant therapy (OAT). Long‐term OAT with vitamin K antagonists (VKA), such as warfarin or phenprocoumon, reduces the risks of stroke and death in patients with atrial fibrillation. Therefore, VKA have been the therapeutic cornerstone for patients with atrial fibrillation at increased thromboembolic risk for decades. Several well‐known drawbacks reduce the efficacy and safety of VKA. First, they increase the risk of bleeding as compared to control therapy.^1^, ^2^ Moreover, VKA have multiple food and drug interactions, and therefore, require frequent laboratory monitoring for optimal dosing. Thus, the rate of discontinuation and side effects is high and many patients receiving VKA still have inadequate anticoagulation (low time within target range regarding international normalized ratio [INR]).^3^, ^4^, ^5^ Indeed, up to half of all these patients which is also true for patients with pulmonary embolism, fail to continuously stabilize their INR within the target range resulting in increased risk for thromboembolism and/or bleeding complications.^6^

Recent years have shown a remarkable evolution in OAT with the emergence of the so‐called nonvitamin K‐dependent oral anticoagulant drugs (NOACs). The first‐in‐class representative of the NOACs was Rivaroxaban. A randomized trial in patients with atrial fibrillation (ROCKET‐AF) revealed noninferiority for Rivaroxaban compared to VKA‐based oral anticoagulation in terms of stroke prevention or systemic embolism.^3^ Similarly, a large RCT has proven noninferiority of Rivaroxaban compared to VKA in patients with deep vein thrombosis or pulmonary embolism.^7^

### The role of vitamin antagonists in the promotion of vascular calcification

1.1

Matrix Gla‐protein (MGP), a vitamin K‐dependent protein, was identified in the human arterial wall and cartilage where the major biological function is the prevention of ectopic calcification. To be fully biologically active, MGP requires vitamin K for posttranslational modification (gamma‐carboxylation in a similar way like the clotting factors II, VII, IX, and X). These anticalcification properties were convincingly demonstrated in MGP‐knockout mice that die from massive aortic calcification (vascular “fracture”) shortly after birth.^4^

Several studies have suggested that treatment with a VKA can increase the rate of development of coronary and valvular arterial calcification,^8^, ^9^, ^10^ whereas the intake of Vitamin K was, in some studies, associated with a slowing of the progression of calcification.^5^, ^11^

Epidemiological, experimental in vivo, and noninterventional human data have supported the theory that vitamin K is essential for the physiological function and phenotype of all human tissues, which should be protected from ectopic calcification. This is especially evident in the tunica media of the vascular wall and the cartilage.^5^ Hence, an important possible side effect of VKA is induction and/or accelerated progression of coronary and valvular calcification.^6^, ^12^, ^13^ Rivaroxaban, on the other hand, inhibits Xa factor without interaction with vitamin K. The COMPASS Trial demonstrated that rivaroxaban plus aspirin compared with aspirin alone reduced the composite endpoint of cardiovascular death, myocardial infarction, or stroke.^14^

In recent years smaller prospective trials have attempted to investigate the differential effects of VKA on calcification. Win et al. found that in comparison to Rivaroxaban, a 52‐week course or warfarin increased plaque volume and calcification as measured by MultiSlice CT (MSCT).^15^ The same group showed that similar effects were obtained with apixaban after 52 weeks compared to warfarin.^16^ This may suggest that the use of a NOAC as OAT may prevent the development of coronary calcification compared to VKA, however, both studies were single centered and included less than 50 patients per group for a relatively short follow‐up period of 52 weeks. Similarly, there have been smaller studies comparing the development of valvular calcification showing a protective effect of NOAC therapy compared to VKA in murine models.^17^ A retrospective study comparing patients on VKA and NOAC also found VKA therapy to be significantly associated with faster progression rates of hemodynamic and anatomic aortic stenosis severity.^18^

In summary, there is currently some evidence from murine and smaller trials, that the use of NOACs may reduce vascular and valvular calcifications compared to VKA therapy in patients on OAT. However, most of the trials were either retrospective or included smaller numbers of patients or shorter duration of follow‐up. The influence of rivaroxaban compared to vitamin K antagonist treatment upon development of cardiovascular calcification in patients with atrial fibrillation and/or pulmonary embolism (IRIVASC) Trial is aiming to definitively answer this question by including around 200 patients followed up for 2 years.

## METHODS

2

### Trial design

2.1

The IRIVASC study is a multicenter, prospective interventional trial randomizing patients with atrial fibrillation or pulmonary embolism requiring long‐term OAT into two different treatment regimens: VKA versus rivaroxaban. VKA dosage was adjusted according to a target INR level of 2.0–3.0. The rivaroxaban dosage was chosen according to official labeling depending on renal function (15 mg once daily for patients with estimated glomerular filtration rate (eGFR) < 30 ml/min/1.73² and 20 mg once daily for patients with eGFR ≥ 30 ml/min/1.73²). The study had an open‐label design. At initiation the study only enrolled patients with a de‐novo indication for OAT; after amendment # 2 (date November 09, 2013) patients with pre‐existing OAT were also approved for inclusion.

Three German study centers participated in the IRIVASC trial: the University Hospital RWTH Aachen (UKA), the Sankt‐Antonius Hospital Eschweiler (SAH), and the Klinikum Coburg. The recruitment was competitive. The randomization was performed 1:1. The treatment was unblinded and INR level controls were done both at the study center during follow‐up visits as well as at the patient's primary care physicians.

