### Conduct of the trial

2.5

After evaluation of inclusion and exclusion criteria and after written informed consent the patients were randomized to two arms (1:1):

Arm A: Rivaroxaban (tablet) with 20 mg once daily for patients with atrial fibrillation with eGFR > 49 ml per minute and 15 mg rivaroxaban once daily for patients with eGFR of 15–49 ml. Rivaroxaban (tablet) for patients with pulmonary embolism: 2× a day 15 mg at Days 1–21 and 1 × 20 mg from Day 22.

Arm B: Adjusted dose coumadin/phenprocoumon (tablet) titrated according to target INR with a target range of 2.0–3.0 according to ACC/AHA/ESC guidelines.^2^

To limit the number of study patients and to detect a sufficient progression of coronary artery or aortic valve calcification within the follow‐up period of 2 years, this study was limited to high‐risk patients defined by baseline calcium AS > 50 (either coronary or valvular).

This threshold ensures a measurable progression in outmost patients as the progression of valvular and coronary calcification is dependent on the baseline calcium load (23–25).

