## RESULTS

3

In total 192 patients were recruited between 2013 and 2018. Of these, baseline data is available for 188 patients (95 in the Phenprocoumon group and 93 in the Rivaroxaban group). The median age of the patients was 72 (IQR 67–76) in the Phenprocoumon group and 68 (IQR 65–75) in the Rivaroxaban group. Within the groups, there were 73.6% and 69.9% male patients, respectively. The main indication for anticoagulation was atrial fibrillation (95.8% and 96.8%, respectively) with pulmonary embolism being the only other indication (Table 1). In total, data for 164 patients (82 patients per group [85%]) is available at 12 months follow up and for 91 patients (45 in the Rivaroxaban group [47%] and 46 [48%] in the Phenprocoumon group). We expect the results of the study to be ready for publication by the end of 2022.

**Table 1 clc23819-tbl-0001:** Characteristics of the patients at baseline (IRIVASC)

	Phenprocoumon (*N *= 95)	Rivaroxaban (*N* = 93)
Median age (IQR), year	72 (67–76)	68 (65–75)
Male, no. (%)	70 (73.6)	65 (69.9)
Diabetes mellitus, no. (%)	23 (24.7)	26 (29.2)
Smoker, no. (%)	11 (11.5)	14 (15)
Non smoker, no. (%)	39 (41)	45 (48.3)
Ex. smoker, no. (%)	42 (44.2)	28 (30.1)
Previous MI, no. (%)	25 (26.3)	26 (27.9)
Previous stroke, no. (%)	16 (16.8)	8 (8.6)
Coronary heart disease (CHD), no. (%)	51 (54.8)	54 (60.6)
Median systolic blood pressure, right (IQR), mmHg	130 (120–143,7)	135,5 (122,7–149)
Median systolic blood pressure, left (IQR), mmHg	130 (120–140)	134 (124–145)
Median total cholesterol (IQR), mg/dl	173 (149.7–204.2)	176 (142–214.5)
Median LDL‐cholesterol (IQR), mg/dl	109 (85.5–128,5)	102.5 (82–138)
Median GFR (IQR), ml/min/1.73 m^2^	65.6 (52.8—81.5)	72.3 (57.2–84.7)
Median hemoglobin (IQR), g/dl	13.9 (13.2–15.2)	14.2 (13.1–15)
Median CHA2DS2VASc score (IQR)	3 (3–4)	3 (2–4)
Indication for anticoagulation:		
1. Atrial fibrillation, no. (%)	91 (95.8)	90 (96.8)
2. Pulmonary embolism, no. (%)	4 (4.2)	3 (3.2)
Type of atrial fibrillation		
1. Paroxysmal, no. (%)	51 (56)	57 (63.3)
2. Persistent, no. (%)	15 (16.5)	14 (15.6)
3. Permanent, no. (%)	16 (17.6)	15 (16.7)
4. New onset, no. (%)	1 (1.1)	1 (1.1)
5. Not further classified, no. (%)	8 (8.8)	3 (3.3)

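### Sections 2.1 and 2.5 state incompatible renal dose boundaries for rivaroxaban in atrial fibrillation, so the assigned dose differs at eGFR 30–49

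*Protocol article*

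**What the plan says.** Section 2.1 (Trial design) gives a complete two-band rule for the rivaroxaban arm: "15 mg once daily for patients with estimated glomerular filtration rate (eGFR) < 30" and "20 mg once daily for patients with eGFR ≥ 30". It does not separate the indications, and it gives the basis of the rule: "The rivaroxaban dosage was chosen according to official labeling depending on renal function".

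Section 2.5 (Conduct of the trial) defines Arm A. Its upper band, for atrial fibrillation, is "20 mg once daily for patients with atrial fibrillation with eGFR > 49 ml per minute". Its lower band is worded as follows: "15 mg rivaroxaban once daily for patients with eGFR of 15–49 ml". For pulmonary embolism it gives a separate schedule with no renal criterion: "2× a day 15 mg at Days 1–21 and 1 × 20 mg from Day 22".

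Neither section is marked as superseded or as applying to a particular period. The only amendment described, amendment 2 in section 2.1, opened the trial to patients already on oral anticoagulation and does not mention dosing.

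On the mix of indications, the Results state: "The main indication for anticoagulation was atrial fibrillation (95.8% and 96.8%, respectively". Table 1 gives 90 patients with atrial fibrillation and 3 with pulmonary embolism in the rivaroxaban arm.

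**The concern.** The rule that sets the dose is part of the definition of the experimental treatment. Here it is stated twice, with two different cut-points, and the cut-points disagree over a range of renal function that patients in this trial could well have.

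The stakes lie in safety reporting and adherence. Bleeding is documented at every visit (section 2.6). A reader of the article cannot tell which dose a patient with moderately reduced renal function should have received, and so cannot tell a protocol deviation from correct dosing or read the bleeding data in that subgroup with confidence. The Discussion names chronic kidney disease among the groups that might gain from avoiding vitamin K antagonists, so these patients will attract attention.

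**Working it through.** No sample size or error rate enters into this. The check sets the two rules side by side over eGFR and then asks how many patients could lie where they disagree.

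**Step 1. Atrial fibrillation (90 of 93 in the arm).**

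| eGFR | Section 2.1 | Section 2.5 | Result |
|---|---|---|---|
| below 15 | 15 mg once daily | no dose stated | not comparable |
| 15–29 | 15 mg once daily | 15 mg once daily | agree |
| 30–49 | 20 mg once daily | 15 mg once daily | conflict |
| above 49 | 20 mg once daily | 20 mg once daily | agree |

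**Step 2. Pulmonary embolism (3 of 93).** From Day 22, both sections give 20 mg once daily at eGFR 30 or above, so there is no conflict at 30–49 in that phase. The sections differ below 30 (15 mg in section 2.1, 20 mg in section 2.5). They also differ on Days 1–21, because section 2.1 has no twice-daily phase.

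**Step 3. How many patients could be in the 30–49 band.** The article gives no count, so this is an estimate. The inputs are the rivaroxaban column of Table 1: median GFR 72.3, IQR 57.2–84.7, N = 93.

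Assume a normal distribution and count values from 30 up to 50:

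- SD = (84.7 − 57.2) / 1.349 = 27.5 / 1.349 = 20.4
- z at 50 = (50 − 72.3) / 20.4 = −1.09; z at 30 = (30 − 72.3) / 20.4 = −2.07
- P(30 to 50) = Φ(−1.09) − Φ(−2.07) = 0.118
- 0.118 × 93 = 11.0 patients; for atrial fibrillation only, 0.118 × 90 = 10.6

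Fitting the SD to the lower half of the distribution only gives about 22.4 and a share of about 13%, or 0.13 × 93 ≈ 12. The estimate is not sensitive to that choice.

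Without a distributional assumption, the lower quartile says only that about a quarter of the arm has GFR below 57.2, and 0.25 × 93 = 23.25. All of these patients could lie between 50 and 57.2, or all between 30 and 49. The reported figures therefore bound the count between 0 and about 23.

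**Step 4. Units.** Section 2.1 indexes eGFR to body surface area, section 2.5 writes millilitres per minute and then only millilitres, and Table 1 uses the indexed form.

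**The case against.** The strongest reply is that this article condenses a full protocol approved by the ethics committee. Sites would have dosed from that protocol, and deviations would be judged against it. On this view section 2.1 is a parenthesis in an overview, section 2.5 is the actual arm definition, and the discrepancy is a slip in a publication that appeared after recruitment had ended in 2018.

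Part of this stands. Leaving the pulmonary embolism schedule out of section 2.1 could be ordinary shortening, and it concerns 3 patients. That section 2.1 sets no lower eGFR limit, while section 2.5 is silent below 15, cannot be held against the plan: the exclusion criteria are in Supporting Information that is not shown and may contain a renal limit. The same caution applies to the pulmonary embolism difference below 30. The unit difference may be shorthand, since section 2.5 shortens its own unit within one sentence.

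The reply does not remove the main point. Section 2.1 does not abbreviate the rule in section 2.5. It states a different one that covers every eGFR value, and each section gives its boundary consistently on both sides. Condensing a protocol explains an omission, but not two incompatible thresholds.

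A reader might also infer that patients were given the wrong dose, or that the trial's main result is compromised. The documents support neither. They contain no dispensing data, and neither section reports doses actually given patient by patient. The primary model in section 2.9 has treatment, visit, baseline measurement and the treatment-by-visit interaction as fixed effects, with random intercepts for participants. Dose and renal function are not terms in it.

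**Conclusion.** The contradiction holds for patients with atrial fibrillation at eGFR 30–49, and nothing in the article explains it. It needs correcting because it concerns a dose threshold that defines the experimental arm and bears on safety.

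The number affected is unknown. The estimate of about 11 of 93 rests on an assumed normal distribution of baseline GFR. It also takes no account of changes in renal function during follow-up.

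The pulmonary embolism differences and the inconsistent units are secondary notes. The finding goes no further than the text: which rule was applied in practice is not shown, no misdosing is shown, and the primary calcification comparison is unchanged whichever rule was in force. Which dose is right is not judged here.

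**What to change.** Reconcile sections 2.1 and 2.5 against the approved full protocol. State one rule in one place, with one eGFR unit and the pulmonary embolism regimen beside it, and have the other section refer to it. No dose or threshold is proposed here.

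Then check the rivaroxaban arm's dispensing records against that rule. If any patient's dispensed dose departed from it, list the case as a protocol deviation and report it alongside the bleeding results. If there were none, say so in a sentence.

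The cost is a short correction to the article and a record check. The check has to cover the whole rivaroxaban arm (93 patients with baseline data), because the patients in the band must first be identified. It should cover follow-up as well as baseline, since eGFR can change over 24 months. The sample size and the primary analysis need no change.

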### STUDY OBJECTIVES

2.2

*The primary endpoint* is the *p*rogression of coronary and aortic valve calcification (quantified by the calcification volume score) as assessed by cardiac computed tomography (CT) at 24 months. The secondary objectives can be found in the Supporting Information Material.

### ETHICS

2.3

The ClinicalTrials.gov Identifier is NCT02066662 and the EudraCT # is 2012‐003768‐28.

The study protocol has been approved by the RWTH Aachen Ethics Committee (UK Aachen EC' EK 239/12). The investigator followed all appropriate requirements, including Good Clinical Practice and Federal Regulation.

### Patient recruitment and evaluation

2.4

Patients with the following criteria were included in the trial:
(i)Adults with need for long‐term OAT according to current international guidelines for the treatment of atrial fibrillation (American College of Cardiologists (ACC)/American Heart Association (AHA)/European Society of Cardiology (ESC)‐guidelines) and/or pulmonary embolism (ACCP/ESC guidelines).(ii)Existent coronary or valvular calcification, or both and an Agatston Score (AS) > 50 in at least one location as assessed by MSCT at screening.

The exclusion criteria can be found in the Supporting Information Material.

### Conduct of the trial

2.5

After evaluation of inclusion and exclusion criteria and after written informed consent the patients were randomized to two arms (1:1):

Arm A: Rivaroxaban (tablet) with 20 mg once daily for patients with atrial fibrillation with eGFR > 49 ml per minute and 15 mg rivaroxaban once daily for patients with eGFR of 15–49 ml. Rivaroxaban (tablet) for patients with pulmonary embolism: 2× a day 15 mg at Days 1–21 and 1 × 20 mg from Day 22.

Arm B: Adjusted dose coumadin/phenprocoumon (tablet) titrated according to target INR with a target range of 2.0–3.0 according to ACC/AHA/ESC guidelines.^2^

To limit the number of study patients and to detect a sufficient progression of coronary artery or aortic valve calcification within the follow‐up period of 2 years, this study was limited to high‐risk patients defined by baseline calcium AS > 50 (either coronary or valvular).

This threshold ensures a measurable progression in outmost patients as the progression of valvular and coronary calcification is dependent on the baseline calcium load (23–25).

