### Study limitations

3.1

This study has some limitations. Owing to the different mechanism of action of both drugs, the trial is open‐label. Furthermore, to increase recruitment, the study enrolled and randomized patients currently on OAT. It could have been better to only enroll OAT naïve patients because the difference in duration of OAT therapy before randomization could become a source of bias. Finally, the study only includes patients with a baseline AS of >50 to limit the number of study patients and to detect a sufficient progression of coronary artery or aortic valve calcification within the set follow‐up period, thus potentially limiting the ability to detect smaller differences between the groups.

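### Sections 2.1 and 2.5 state incompatible rivaroxaban regimens for patients with pulmonary embolism

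*Protocol article*

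**What the plan says.** Two sections of the protocol article state the rivaroxaban dose.

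- **Section 2.1, Trial design.** The trial is introduced as "randomizing patients with atrial fibrillation or pulmonary embolism requiring long‐term OAT into two different treatment regimens". The section then says "The rivaroxaban dosage was chosen according to official labeling depending on renal function" and lists two doses: "15 mg once daily for patients with estimated glomerular filtration rate (eGFR) < 30", and 20 mg once daily at an eGFR of 30 or more. It has no twice-daily phase and no exception for embolism.
- **Section 2.5, Conduct of the trial.** Arm A is divided by indication. For fibrillation it gives "20 mg once daily for patients with atrial fibrillation with eGFR > 49 ml per minute" and 15 mg once daily at an eGFR of 15–49. A separate sentence, opening "Rivaroxaban (tablet) for patients with pulmonary embolism", gives "2× a day 15 mg at Days 1–21 and 1 × 20 mg from Day 22". That sentence contains no eGFR rule, no definition of Day 1 and no reference to earlier anticoagulation.

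On who could enter, section 2.1 reports that recruitment began with new indications only and that after amendment 2 "patients with pre‐existing OAT were also approved for inclusion". Section 3.1 (Study limitations) confirms that "the study enrolled and randomized patients currently on OAT". Inclusion criterion (i) in section 2.4 does not restrict embolism to new events.

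**The concern.** A reader who wants to know what an embolism patient in Arm A was to receive gets two answers. Section 2.1 covers embolism patients in its description of the population and then states doses that leave no room for the twice-daily phase in section 2.5. This is two positive statements that disagree, not a detail left out of one section.

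A second, weaker point concerns the regimen in section 2.5 and the population after amendment 2. The article reports that already anticoagulated patients were admitted, but the embolism regimen is stated once for all such patients, with Day 1 undefined. The text does not show whether the 21-day phase was meant for them.

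What is at stake is the description of exposure and the reading of safety data. Section 2.6 has bleeding documented at every visit, and visits fall at 1 week and 1 month, so the disputed three weeks lie inside the safety record. If the assigned dose cannot be established from the text, early bleeding in these patients cannot be related to a known exposure.

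**Working it through.** The article gives no figure of its own for this point. The check is a comparison of text plus simple arithmetic.

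**1. Daily dose on Days 1–21 for an embolism patient in Arm A**

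- Section 2.5: 2 × 15 mg = 30 mg/day.
- Section 2.1, eGFR 30 or more: 1 × 20 mg = 20 mg/day. Difference 30 − 20 = 10 mg/day, or 21 × 10 = 210 mg over the phase.
- Section 2.1, eGFR below 30: 1 × 15 mg = 15 mg/day. Difference 30 − 15 = 15 mg/day, or 21 × 15 = 315 mg over the phase.

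At no eGFR do the two sections agree on these days.

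**2. Daily dose from Day 22**

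- Section 2.5: 20 mg once daily, with no eGFR split in the embolism sentence.
- Section 2.1: 20 mg once daily at eGFR 30 or more, which agrees; 15 mg once daily below 30, which does not.

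The 15 mg clause for eGFR 15–49 in section 2.5 does not repeat the fibrillation qualifier, but it stands in the fibrillation sentence, before the embolism regimen. Whether it was meant to reach embolism patients cannot be read from the text.

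**3. Does the reference to labelling in section 2.1 remove the conflict?** No. The sentence goes on to state its own doses, all once daily and split by renal function alone.

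**4. Patients concerned (Table 1)**

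- Rivaroxaban: 3/93 = 3.2%.
- Phenprocoumon: 4/95 = 4.2%, not affected by the rivaroxaban rule.
- Both arms: 7/188 = 3.7%.

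The figure of 3 is a minimum, because 192 − 188 = 4 randomised patients have no baseline data. The number already anticoagulated at entry is not given; among the 3 with baseline data it can be anything from 0 to 3.

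**5. Patients with both indications.** The indication rows sum exactly to the arm totals (91 + 4 = 95; 90 + 3 = 93), so each patient is counted under one indication. The table therefore neither shows nor rules out patients with both.

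**6. Bearing on the primary endpoint.** The endpoint is at 24 months, about 730 days, so the disputed phase is 21/730 = 2.9% of follow-up in about 3% of one arm. The sample size calculation uses none of this. It reproduces independently: with SD 234, difference 96, two-sided 5% and 80% power, the normal formula gives 94 per group and the t-test version 94.24, rounded up to the stated 95.

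**7. Related conflict in the same two sections.** The renal cut-off is 30 in section 2.1 and 49 in section 2.5, so the stated doses also disagree for a fibrillation patient with an eGFR of 30–49. Fibrillation accounts for 90/93 = 96.8% of the rivaroxaban arm. This is a separate point, but the same edit has to settle it.

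**The case against.** The strongest reply is that this is a condensed article. Section 2.1 is a one-sentence summary, section 2.5 is the detailed account, and sites worked from the full protocol, which is not shown. How an embolism patient already on anticoagulation is handled, and which rule governs a patient with both indications, are details an article may leave to that protocol. Recruitment ended in 2018, so a letter to sites could change nothing.

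Most of this stands. A reader might infer that the 21-day phase runs from the start of trial treatment, so that sites would give it to patients anticoagulated for months or years. The documents do not support that: section 2.5 says only Days 1–21, and Day 1 could be randomisation, the first study dose or the embolic event. Nor do they support an inference that the three sites treated patients differently, or that patients with both indications fell under clashing rules, since no such patient is shown.

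The reply fails on one point. Condensing explains what is left out; it does not explain two incompatible statements of dose for the same patients. Calling one section a summary does not make its stated doses compatible with the other's.

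**Conclusion.** The contradiction between sections 2.1 and 2.5 on the embolism regimen is established from the text and needs no outside source: 30 mg/day against 15 or 20 mg/day on Days 1–21 and, below an eGFR of 30, 20 against 15 mg/day afterwards, if the embolism sentence in section 2.5 is read as it stands, without a renal rule.

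The undefined Day 1 and the silence on embolism patients with prior anticoagulation are ambiguities that the full protocol may resolve. They are not shown to be errors.

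The point is small in number and should have a negligible effect on the calcification endpoint; that judgement assumes that the few patients without baseline data, or with a second indication not shown in Table 1, do not change the picture materially. It matters for stating exposure correctly and for interpreting early safety data. No view is taken on which regimen is right.

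**What to change.** - Reconcile sections 2.1 and 2.5 with the full protocol so that both state the same rivaroxaban regimen for pulmonary embolism, including whether renal function alters it. Settle the eGFR cut-off conflict for fibrillation in the same edit.
- Define what Day 1 counts from, and state whether the Days 1–21 phase applied to embolism patients already on anticoagulation at randomisation.
- In the results report, give the regimen that embolism patients in Arm A actually received, including the number already on anticoagulation at entry.

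The cost is a correction of wording and a short exposure listing for a handful of patients. Sample size, randomisation and the primary analysis are unchanged. Because recruitment is complete, the remedy is accurate text and reporting, not a new instruction to sites.
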